#### Recruitment and procedure

Eligible patients will be identified through the review of participating centers’ clinical charts. A member of the research team will contact them by telephone to explain the study and invite them to participate. Those who agree will complete the baseline assessment in the same phone call, and an appointment will be scheduled with a researcher at their referral primary healthcare center or hospital. There, patients will be asked to read the project information sheet, which will explain in detail what their participation will consist of, and to sign the informed consent. Then, patients allocated to the intervention group will review the PtDA accompanied by a researcher, who will give support in navigation if necessary. Then, they will complete the questionnaires assessing the outcome measures, in the same web interface. Patients in the control group will follow the same procedure, but instead of the PtDA, they will review general information about OA of the hip, knee, ankle, and foot, information included in a brochure delivered in primary care centers of the Canary Islands Health Service, which will be also presented in a web format.

#### Outcome measures

The primary outcome of this study will be decisional conflict regarding the treatment for OA, assessed with the Decisional Conflict Scale (DCS) [18], immediately after reviewing the PtDA. This is a 16-item self-reported scale widely used in PtDA research. It has 5 subscales: feeling informed, values clarity, feeling supported, uncertainty, and effectiveness. Scores are transformed to a 0–100 scale, with higher scores indicating more conflict. In previous studies in other health conditions, we have obtained good internal consistency values (0.88–0.90) [19–21]. The secondary outcomes will include:
Knowledge of the disease and treatments: assessed with a 7-item questionnaire previously used in studies of PtDA in OA, specifically adapted for hip OA [22]. This instrument assesses patients’ objective knowledge as an outcome of the information/decisional process, and it does not measure the level of health literacy. Items have a “true/false/do not know” format. The percentage of correct responses represents the total score.Values about characteristics of treatments: patients will be asked to rate in a 0–10 scale the importance they attribute to different characteristics of treatment: mode of administration, improvement in pain and function, risk of mild and serious adverse effects, time until symptoms’ improvement, duration of benefits, and in the case of arthroplasty, period of rehabilitation and risk of needing surgery revision.Treatment preference (physiotherapy, medication, intra-articular injections, arthroplasty, not sure).Intention to undergo the preferred treatment: assessed with one item ranging 0 (not sure) to 5 (completely sure).Concordance between values and intention to undergo arthroplasty vs. conservative treatments: binary variable (yes/no) derived from the association between values and intention to undergo arthroplasty (see the “Statistical analysis” section).Decision quality about arthroplasty: binary variable (yes/no) defined as a combination of adequate knowledge (≥ 60% of correct responses) and concordance.Satisfaction with the decision-making process: assessed with the 12-item questionnaire developed by Barry et al. [23]. In a previous study with type 2 diabetes patients, we obtained a Cronbach alpha value of 0.90 [20].Safety: patients will be asked whether participation in the study has produced any psychological undesired outcome such as anxiety, mood changes, uncertainty, or any kind of concern.

At baseline, in the telephone call to recruit patients, assessment will include the primary outcome (DCS), as well as the following control variables: sociodemographic (i.e., age, sex, education, living and job status) and clinical data (i.e., comorbidities, affected hip, OA duration, previous and current treatments for OA, being in waiting list for arthroplasty); the Patient Activation Measure (PAM) [24]; and general health-related quality of life measured with the EuroQoL questionnaire (EQ-5D-5L) [25]. Knowledge will be assessed just before the application of the PtDA (or the OA general information in the control group). Immediately after the intervention, all the outcome measures will be assessed again.

#### Sample size calculation

Assuming type I and II errors of 0.05 and 0.20 respectively, a total of 126 patients (63 per group) are needed in order to detect a medium effect size (Cohen’s *d* = 0.5) [26] in the primary dependent variable (DCS). No losses are expected given that the post-intervention assessment will take place immediately after the application of the PtDA.

#### Statistical analysis

Data will be analyzed on an intention-to-treat basis, although given the nature of the intervention, we do not expect relevant protocol deviations. The baseline equivalence of the randomized groups will be assessed by means of Student’s *t* test and *χ*^2^ test, for continuous and categorical variables, respectively. To analyze the effect of the intervention on the primary outcome (DCS), mixed linear regression model with intervention as independent variable will be used, adjusting for DCS baseline scores and sociodemographic or clinical variables which show significant between-group differences at baseline. Center will be included as a random intercept to control for the potential intraclass correlation. The same analysis will be carried out for the remaining continuous outcomes. Treatment preference will be analyzed by means of *χ*^2^ test. Concordance between values and intention to undergo arthroplasty will be calculated by means of a method similar to the one proposed by Sepucha et al. [27]: first, a binary variable will be created, with a value of 1 for participants who prefer arthroplasty and scored 4 or 5 in intention to undergo it, and zero for the remaining patients. Second, a mixed logistic regression model will be performed with patients’ values as independent variables and intention to undergo arthroplasty (vs. other treatments) as dependent variable. Significant predictors will be retained in the model and the predicted score for each patient will be calculated. Patients with a predicted score equal or higher (lower) than 0.5 and intention to (not) undergo arthroplasty will be classified as concordant, and the remaining ones as not concordant. Finally, the effect of the DA in the number of concordant patients, as well as the number who make a quality decision, will be assessed with mixed logistic regression. For all outcomes, we will explore the interaction of the intervention with sex and education. Analyses will be performed with Stata® 15.0.

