#### Randomization and allocation concealment

Computer-based randomization with Stata® 15.0 will be performed centrally by an independent researcher (allocation rate 1:1). Randomization will be stratified by patient inclusion in waiting list for arthroplasty (yes/no). Sealed envelopes with each patient’ allocation will be prepared, which will be opened only after the patient sign the informed consent for participation in the study. The nature of the intervention makes impossible to blind patients and researchers to group allocation.

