### Limitations and strengths

In relation to the systematic review for the development of the PtDA, it is expected to find limitations related to the coverage and completeness of the information obtained, since the bibliographic search does not guarantee the obtaining of the universe of articles. We will expand the search with consultation of other sources such as specialized websites and institutions working in this area of research.

The main limitations of the effectiveness study are the impossibility of blinding participants to treatment allocation, and the absence of follow up, which precludes the assessment of patients’ subsequent interaction with their health care providers and their actual treatment choices. We will try to mitigate the lack of blinding giving control participants a brochure with general information about OA. In the absence of data about patients’ actual decisions, we will measure the intensity of their intention to undergo their prefer treatment. On the other side, we will only collect baseline data for the primary outcome and knowledge, in order to avoid overloading patients with too many questionnaires; nonetheless, an adequate randomization and allocation process should overcome the influence of this limitation.

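### Read literally, the knowledge outcome is adjusted for baseline decisional conflict, and the baseline knowledge score enters no effect model

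*Protocol article*

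**What the plan says.** All references are to the protocol article.

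- **Statistical analysis.** One linear mixed model is specified, for the DCS. It contains the intervention, baseline DCS, any sociodemographic or clinical variable that differs significantly between groups at baseline, and a random intercept for centre. The section continues: "The same analysis will be carried out for the remaining continuous outcomes".
- **Outcome measures.** Knowledge is the first secondary outcome listed. It is a 7-item test scored as percentage correct, so it falls under that sentence. On timing: "Knowledge will be assessed just before the application of the PtDA (or the OA general information in the control group"). It is measured again after the intervention.
- **Limitations and strengths.** To spare patients too many questionnaires, "we will only collect baseline data for the primary outcome and knowledge". DCS and knowledge are therefore the only outcomes with a pre-intervention value.

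**The concern.** The only baseline score named in the model is that of the DCS, and the model is carried over to the other continuous outcomes with no statement that the covariate changes. Knowledge would then be adjusted for a different construct, while its own pre-test, normally the better predictor, is left out. The imbalance rule does not clearly bring it in, because that rule covers sociodemographic and clinical variables and the article lists knowledge apart from both.

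Two things are at stake. The first is precision: a covariate that explains more of the outcome variance gives a smaller standard error at no cost. The second is chance imbalance: if one arm happens to know more at the start, adjustment for baseline DCS will remove little of that difference. The wording also leaves the analyst to choose the knowledge covariate later, in a trial where patients and researchers are not blinded to allocation.

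**Working it through.** **1. The plan's own figure.** Inputs from Sample size calculation: "Assuming type I and II errors of 0.05 and 0.20 respectively"; Cohen's d = 0.5; "a total of 126 patients (63 per group) are needed". Allocation is 1:1 (Randomization and allocation concealment) and no losses are expected. The article does not state sidedness; two-sided is assumed.

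n per group = 2(1.960 + 0.842)² / 0.5² = 2 × 7.85 / 0.25 = 62.8, so 63 per group and 126 in total. The stated figure is reproduced. It concerns the DCS only, so nothing below changes it.

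**2. Effect of the covariate on the standard error.** In a linear model with a covariate that correlates r with the outcome, the residual SD is proportional to √(1 − r²). The right comparison is between the two candidate covariates:

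SE ratio = √[(1 − r_K²) / (1 − r_D²)]

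Here r_K is the correlation of post-intervention knowledge with baseline knowledge, and r_D its correlation with baseline DCS. The article gives neither. Assumed: r_K = 0.3, 0.5 or 0.7, and |r_D| = 0.2.

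- r_K = 0.3: √(0.91/0.96) = 0.974, SE lower by about 3%
- r_K = 0.5: √(0.75/0.96) = 0.884, SE lower by about 12%
- r_K = 0.7: √(0.51/0.96) = 0.729, SE lower by about 27%

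With |r_D| = 0.1 the denominator is 0.99 and the reductions are about 4%, 13% and 28%, so the result is not sensitive to r_D in this range.

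**3. The same in terms of power.** With 63 per group and an illustrative d = 0.5 on knowledge (the article sets no target for this outcome), and detectable d = (1.960 + 0.842) × √(1 − r²) × √(2/63):

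| Covariate | Assumed r | Power | d detectable with 80% power |
|---|---|---|---|
| Baseline DCS | 0.1 | 0.805 | 0.497 |
| Baseline DCS | 0.2 | 0.817 | 0.489 |
| Baseline knowledge | 0.3 | 0.837 | 0.476 |
| Baseline knowledge | 0.5 | 0.900 | 0.432 |
| Baseline knowledge | 0.7 | 0.976 | 0.356 |

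**4. Check on validity.** Simulated trials of 126 patients (4,000 replicates per scenario, no centre effect) gave type I error of 0.041 to 0.053 with baseline DCS as covariate and 0.049 to 0.055 with baseline knowledge. Both are close to 0.05. Simulated power was 0.79 to 0.81 with baseline DCS, against 0.82, 0.89 to 0.90 and 0.97 with baseline knowledge at r_K = 0.3, 0.5 and 0.7. Either covariate gives a valid test; they differ in precision.

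**The case against.** The strongest reply is that the literal reading is unkind. A paragraph about the DCS model naturally names the DCS baseline, and calling the other analyses the same is common shorthand for the same model with outcome and baseline swapped. Limitations and strengths supports this: it pairs DCS and knowledge as the outcomes with baseline data and treats the lack of baselines elsewhere as a limitation, which suggests that each baseline was meant to serve its own outcome. Covariate lists for secondary outcomes are also often left to an analysis plan, which is not shown here.

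The intention is plausible, and that part stands. It does not settle the matter. The article is not silent: it names a covariate and extends the model. The own-baseline reading cannot be carried out for satisfaction, strength of intention or the value ratings, which have no baseline, so some further unwritten rule is needed in any case.

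Four stronger readings are tempting, and the documents do not support them:

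- **That the pre-test is used nowhere.** The planned t tests of baseline equivalence may well include it. What can be said is that it enters no stated effect model.
- **That the decision-quality analysis is wrong for the same reason.** The article names no covariates for its mixed logistic models, so no wrong one is fixed there. The √(1 − r²) formula is also a linear-model result and does not carry over to a binary composite.
- **That the loss amounts to about half the sample.** At r_K = 0.7, 1/(1 − 0.49) − 1 gives 96% more patients, but that compares with no adjustment, whereas the plan does adjust for baseline DCS. It also takes the top of an assumed range, and a high correlation is doubtful for seven items that the intervention is meant to change.
- **That the knowledge comparison is biased.** Randomization protects it on average under either covariate.

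**Conclusion.** The point holds as a specification defect on one secondary outcome. As written, post-intervention knowledge is adjusted for baseline DCS, and the baseline knowledge score that patients are asked to provide has no stated role in any effect model.

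The size depends on correlations that the article does not give. Over the assumed range the gain in standard error runs from negligible (about 3%) to substantial (about 27%), with about 12% in the middle. Baseline knowledge is the better single covariate whenever it correlates more strongly with later knowledge than baseline DCS does. That is very likely, but it is an assumption.

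Type I error, average unbiasedness, the primary DCS analysis and the sample size of 126 are not affected. The change is worth making because it is a free improvement on the stated rule, not because the stated rule is invalid.

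**What to change.** In Statistical analysis, add a statement to this effect: the knowledge model adjusts for the pre-intervention knowledge score, in place of or in addition to baseline DCS; and for continuous outcomes without their own baseline (satisfaction, strength of intention, value ratings) the covariates are listed explicitly. Whether baseline DCS is kept for that second group is for the authors to decide; it only needs to be stated before the outcome data are analysed.

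The cost is one or two sentences. The pre-test is already collected, and neither the sample size nor the primary analysis changes. Adjustment for the waiting-list stratification factor is a separate question and need not be settled here.

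### Treatment preference is tested with an unstratified five-category chi-square although randomisation is stratified by the arthroplasty waiting list, which costs power if the list predicts preference (minor)

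*Protocol article*

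**What the plan says.** The Outcome measures section lists the secondary outcome with its response options: "Treatment preference (physiotherapy, medication, intra-articular injections, arthroplasty, not sure". That is five unordered categories, and one of them is arthroplasty.

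The Randomization and allocation concealment section gives "allocation rate 1:1" and continues: "Randomization will be stratified by patient inclusion in waiting list for arthroplasty (yes/no". It states no blocks or other restriction within strata.

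The Statistical analysis section says "Treatment preference will be analyzed by means of" a chi-square test, with no stratum, covariate or centre term. Continuous outcomes get a mixed linear model with a random intercept for centre. Concordance and decision quality get mixed logistic regression. The same paragraph promises to explore, for every outcome, whether the intervention effect varies with sex and education.

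The sample size section covers only the Decisional Conflict Scale: "a total of 126 patients (63 per group) are needed", for an effect "in the primary dependent variable (DCS". No effect or power is claimed for preference.

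**The concern.** The waiting list is a list for one of the five answers to the question, and the trial enrols both surgical and non-surgical candidates. Patients on the list may well choose arthroplasty far more often than the others. A pooled chi-square treats this between-stratum difference as chance variation, so its yardstick is too wide and a real effect of the decision aid on preference is harder to see. A non-significant result would then be hard to read.

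A second, smaller point needs no assumption. A two-way chi-square cannot supply the interactions with sex and education that the same paragraph promises for all outcomes.

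**Working it through.** **Inputs from the protocol.** Two arms, 1:1; N = 126; five categories; two strata; alpha 0.05. The share of patients on the list, its link to preference and the expected effect on preference are not given. They are assumptions below.

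**The plan's own figure.** For d = 0.5, two-sided alpha 0.05 and power 0.80, n per arm = 2(1.960 + 0.842)²/0.5² = 62.8, so 63 per arm and 126 in total. This reproduces the sample size section. It concerns the primary outcome only. (The Abstract gives 124; the difference does not matter here.)

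**The two tests.**
- Planned: X² = Σ(O − E)²/E over the pooled 2×5 table, with E = row total × column total / N and (2 − 1)(5 − 1) = 4 degrees of freedom.
- Stratified (Cochran-Mantel-Haenszel general association): Q = d′V⁻d, where V⁻ is a generalised inverse. Here d sums over strata the observed minus expected counts in one arm, and V = Σₕ n₁ₕn₂ₕ/(Nₕ − 1) × [diag(pₕ) − pₕpₕ′], with pₕ the category proportions in stratum h. It also has 4 degrees of freedom, so the two tests ask the same question.

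**Why pooling costs power.** Assume 50 patients on and 76 off the list. Arthroplasty preference is 90% (control) against 75% (intervention) on the list, and 35% against 15% off it. Consider the arthroplasty category alone.
- Mean preference is 0.825 on the list and 0.25 off it. Overall it is (50 × 0.825 + 76 × 0.25)/126 = 60.25/126 = 0.478.
- Pooled variance: 0.478 × 0.522 = 0.250.
- Within-stratum variance: (50 × 0.825 × 0.175 + 76 × 0.25 × 0.75)/126 = (7.22 + 14.25)/126 = 0.170.
- Ratio: 0.170/0.250 = 0.68. About a third of the variation that the pooled test counts as noise is the difference between strata.

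**Simulation of this scenario** (25 + 25 on and 38 + 38 off the list; other answers split 0.4/0.3/0.1/0.2). Power is about 30% for the planned test and about 48% for the stratified five-category test. Repeat runs move these by up to about three percentage points.

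**Level of the planned test.** Under a null of 85% on and 25% off the list, it rejects in about 3.3% of trials when allocation is balanced within strata. With unrestricted allocation within strata it rejects in about 5.2%. The power loss remains in that case: 33% against 47%.

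**Range over the unknown link.** 3,000 trials per cell; list share 25% or 50%; exact balance within strata; effect = odds ratio 3 for arthroplasty in both strata. Both tests keep five categories.

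| Control preference for arthroplasty, on/off list | Level, planned | Power, planned | Power, stratified |
|---|---|---|---|
| 25%/25% (none) | 0.047 | 0.65–0.66 | 0.64–0.65 |
| 60%/12% (moderate) | 0.040–0.042 | 0.35–0.37 | 0.48–0.49 |
| 84%/6% (strong) | 0.024–0.028 | 0.07–0.08 | 0.24–0.26 |
| 95%/2% (extreme) | 0.020–0.023 | 0.02–0.03 | 0.07 |

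With unrestricted allocation the level stays at 0.044–0.053. Power at odds ratio 3 is then 0.36–0.38 against 0.46–0.47 (moderate) and 0.12–0.15 against 0.24 (strong).

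**What collapsing to arthroplasty versus other would do.** In the 90/75 and 35/15 scenario, the stratified two-category test has about 69% power. Now hold arthroplasty preference fixed at 85%/25% and move only the other answers (physiotherapy, medication, injections, not sure) from 0.25/0.30/0.10/0.35 to 0.55/0.25/0.10/0.10. The planned test has about 62% power, the stratified five-category test about 64% and the two-category test 4.6%.

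**The case against.** The protocol powers only the Decisional Conflict Scale. Preference is one of several secondary outcomes, and an omnibus test without a direction is a defensible choice for it. The primary model does not name the waiting-list stratum either, so the omission is not peculiar to this outcome. The promised interactions suggest that some further analysis of preference is foreseen. All of this stands, and it limits the weight of the point.

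Several stronger readings are tempting, and the protocol does not support them.
- *The waiting list largely determines preference.* No share or association is given, and with no association nothing is lost.
- *The test is over-conservative.* That needs balance within strata, for example from blocks, and none is stated.
- *Ignoring the strata costs the whole gap from about 29% to about 69%.* That comparison also collapses five categories to two, under an alternative that moves only arthroplasty. Like for like, the gap is about 30% to 48%.
- *Arthroplasty versus other is the contrast that matters here.* The protocol does not say so for this outcome. It already carries that contrast through concordance and decision quality. A decision aid could plausibly act by reducing the 'not sure' answers, which the two-category test would miss.
- *No estimate or interval will be reported.* Naming a chi-square test does not exclude them, and a protocol article commonly leaves such detail to the full plan.

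**Conclusion.** The point holds as a minor matter of efficiency. The protocol fixes a pooled chi-square for an outcome of which one category is tied to the randomisation stratum. A test of the same five categories, stratified by waiting list, is materially as good when the stratum is irrelevant and better when it is not. In the main assumed scenario the gain is from about 30% to about 48% power. Across the range examined it runs from nothing to roughly a threefold difference, and with strong dependence even the stratified test has only about 25% power at odds ratio 3.

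A reader might infer that the planned p-value is invalid. It is not: at worst the test runs below its nominal level, and only under within-stratum balance. The sizes rest on the assumed list share, preferences and effects. The direction of the power loss rests only on the list predicting preference.

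**What to change.** In the Statistical analysis section, replace the plain chi-square with a five-category Cochran-Mantel-Haenszel general association test stratified by waiting list. Alternatively, use a multinomial model with the stratum as covariate. The model could also supply the interactions with sex and education that the section promises, although sparse categories (not sure, injections) may make those estimates unstable with about 63 patients per arm.

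An arthroplasty-versus-other contrast adjusted for waiting list, with its odds ratio and interval, may be added and labelled supportive. It should not replace the five-category test, because it cannot see shifts among the conservative options or out of 'not sure'.

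The cost is a sentence of text and a different command. Waiting-list status is already collected at baseline, so no extra data or patients are needed. The change should be made before outcome data by arm are examined.

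### The concordance rule codes patients with no treatment preference as not intending arthroplasty, so they can count as value-concordant and as having made a quality decision

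*Protocol article*

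**What the plan says.** Under Outcome measures, preference has five options, the last being no choice: "Treatment preference (physiotherapy, medication, intra-articular injections, arthroplasty, not sure". Strength of intention towards the preferred treatment is "assessed with one item ranging 0 (not sure) to 5 (completely sure".

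The same section names the concordance outcome "Concordance between values and intention to undergo arthroplasty vs. conservative treatments" and refers to Statistical analysis for its derivation. There the intention variable equals 1 for "participants who prefer arthroplasty and scored 4 or 5 in intention to undergo it, and zero for the remaining patients". It is then regressed on the patients' ratings of treatment characteristics, with "intention to undergo arthroplasty (vs. other treatments) as dependent variable". The classification rule follows: "Patients with a predicted score equal or higher (lower) than 0.5 and intention to (not) undergo arthroplasty will be classified as concordant".

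Decision quality is "defined as a combination of adequate knowledge" (at least 60% correct) and concordance. Both outcomes are compared between arms by mixed logistic regression. Nothing in the protocol excludes patients without a preference from these outcomes or gives them a category of their own.

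**The concern.** The zero code mixes three groups: patients who prefer a conservative treatment, patients who prefer arthroplasty but score 0 to 3 on intention, and patients who state no preference. The third group has not chosen anything, yet the rule can credit its members with a choice that matches their values and, given enough correct knowledge answers, with a good decision. For these patients the intention item has no preferred treatment to refer to.

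Two things follow. First, concordance and decision quality are inflated in any arm that contains such patients. Second, the decision aid is intended to help patients reach a decision, so the share without a preference may differ between arms after the intervention. If it does, the arm comparison partly compares how many undecided patients each arm contributes as successes. In addition, coding these patients as zero in the values model pulls predicted scores down, which makes a score below 0.5 more common.

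**Working it through.** **The plan's own figure.** No figure is given for concordance or decision quality. The only sample size is for the primary outcome (Sample size calculation: d = 0.5, errors 0.05 and 0.20, 63 per group). It reproduces: 2 × (1.960 + 0.842)² / 0.5² = 62.8, so 63 per group and 126 in total. It does not depend on the point made here.

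**Tracing the rule.** Inputs are the preference and intention items (Outcome measures) and the coding and 0.5 cut-off (Statistical analysis).

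| Preference | Intention | Code | Predicted score | Class |
|---|---|---|---|---|
| Arthroplasty | 4–5 | 1 | ≥ 0.5 | concordant |
| Conservative option | 0–5 | 0 | < 0.5 | concordant |
| Arthroplasty | 0–3 | 0 | < 0.5 | concordant |
| Not sure | any | 0 | < 0.5 | concordant |
| Not sure | any | 0 | ≥ 0.5 | not concordant |

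The knowledge cut-off with 7 items: 4/7 = 57.1% fails and 5/7 = 71.4% passes. A patient in the fourth row with five correct answers is therefore recorded as having made a quality decision.

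**Effect on the arm difference (assumed inputs).** Let u be the share undecided in an arm and q the share of them with a predicted score below 0.5. Holding predicted scores fixed, the rule adds u × q to that arm's concordance compared with classing these patients as not concordant. The shift in the difference (intervention minus control) is (u_int − u_ctl) × q.

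- Undecided 20% control, 10% intervention: −0.10 × 0.6 = −6 points; −0.10 × 1.0 = −10 points.
- Shares reversed: +6 to +10 points.
- Equal shares: no shift in the difference, but both arms are inflated.

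For decision quality the added share is multiplied further by the proportion of these patients who pass the knowledge cut-off.

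**A fuller illustration.** Assume 75% concordance among decided patients in both arms, with 30% undecided in control and 10% in intervention.

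- Undecided classed as not concordant: 0.70 × 75% = 52.5% versus 0.90 × 75% = 67.5%, a difference of +15 points.
- Rule as written: the difference is (0.30 − 0.10) × (0.75 − q), that is +5, +1 or −3 points for q = 0.5, 0.7 or 0.9.

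**How large might q be?** In a simulation with assumed inputs (126 patients, one values score with log-odds 1.5 per SD, probability of wanting arthroplasty at the average score 20% to 50%, 10% to 30% undecided, no centre effect), 58% to 94% of undecided patients were classed as concordant. Overall concordance was 70% to 82% as written, against 47% to 71% when undecided patients counted as not concordant. These ranges show that the mechanism can be material. They are not estimates for this trial.

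**The case against.** The best defence is that the outcome concerns arthroplasty, yes or no. Outcome measures hands the working definition to Statistical analysis, and a patient not committed to elective surgery is, plainly read, not intending it. A reader might infer that the rule contradicts the outcome's definition. Because of that cross-reference, the text supports only a mismatch between the named contrast and the coding.

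A reader might also infer that every patient in the zero group with intention below 4 has made no decision. The item measures certainty about the preferred treatment, and only its zero point is labelled as unsure. Someone who prefers physiotherapy with a score of 3 may be quite clear about not wanting surgery. This part of the defence stands, so failing all such patients in the main analysis would be debatable.

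A third tempting reading is that the rule gives no credit for resolving indecision and is therefore biased against the decision aid. That is too strong. A 'not sure' patient with a predicted score of 0.5 or more is not concordant, and becomes concordant on moving to firm arthroplasty. Credit is lost only for a patient predicted below 0.5 who moves to a conservative choice. The direction of any distortion depends on shares by arm that the documents do not give.

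Finally, indecision is captured elsewhere: the DCS has an uncertainty subscale, intention is analysed as a continuous outcome, and preference is compared by χ² test. A reduction in indecision would thus be seen. This limits the harm but does not make the two derived outcomes mean what their names say.

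**Conclusion.** The point holds for patients without a stated preference: the written rule can count them as concordant and as quality decision-makers, and no other part of the protocol corrects this. The protocol fixes this rule itself, so the point is not about detail left to an analysis plan. Patients who prefer arthroplasty with low intention are affected by the same coding, but how they should be classed is more open.

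Concordance and decision quality are inflated wherever such patients occur with predicted scores below 0.5. The arm difference is distorted only if the undecided share, or the fraction of those patients predicted below 0.5, differs by arm. The figure of −6 to −10 points rests entirely on the assumed 20% versus 10% and on q of 0.6 to 1.0; other shares give a smaller, larger or opposite shift. Both outcomes are secondary, and the DCS analysis and the sample size stand. The change is worth making because it is cheap and can be settled before analysis.

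**What to change.** In the main analysis, fit the values model only on patients who state a treatment preference. Class patients whose preference is 'not sure' as not concordant and not a quality decision. Keep all randomised patients in the comparison between arms, in line with the stated intention-to-treat principle.

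Report three sensitivity analyses:

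- (a) the rule as now written;
- (b) decided patients only, read with caution because being decided is itself observed after randomisation;
- (c) one certainty threshold, intention 4 to 5, applied to arthroplasty and conservative choices alike. This shows how much rests on patients with low intention, including those who prefer arthroplasty at 0 to 3, who keep code 0 in the main analysis.

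The cost is a few sentences of outcome definition and no new data. There are three downsides to state openly. Absolute concordance rates will fall. The outcome will partly reflect decidedness as well as match with values, so it should be read beside the treatment-preference comparison. The values model will be fitted on fewer patients: with an assumed 10% to 30% undecided, about 113 to 88 of 126 (126 × 0.9 and 126 × 0.7), for the 7 to 9 candidate ratings listed under Outcome measures, depending on how the paired items are counted.
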